**Methods:**

We will conduct a parallel randomized controlled pilot study at the Friedrich-Alexander-Universität Erlangen-Nürnberg, Germany. Individuals with elevated stress levels will be randomized to one of eight study conditions (*n* = 10 per condition) — one of six variants of the eAAMT, an active control intervention (swipe-based AAMT), or an inactive control condition. Participants in the intervention groups will engage in four sessions of 20–30 min (e)AAMT training on consecutive days. Participants in the inactive control condition will complete the assessments via an online tool. Non-blinded assessments will be taken directly before and after the training and 1 week after training completion. The primary outcome will be perceived stress. Secondary outcomes will be dysfunctional beliefs, symptoms of depression, emotion regulation skills, and physiological stress measures. We will compute effect sizes and conduct mixed ANOVAs to explore differences in change in outcomes between the eAAMT and control conditions.

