## Methods

### Design

We will conduct a parallel eight-armed randomized controlled pilot study (see Fig. 1 for the study flow and supplemental materials for the spirit checklist of the trial). The study will be conducted at the Department of Clinical Psychology and Psychotherapy of the Friedrich-Alexander-Universität Erlangen-Nürnberg. In the eAAMT and swipe control groups, participants will receive four sessions à 20–30 min of training on four consecutive days, while the inactive control group will not receive any training. Participants will be randomly assigned to one of the eight study groups with a 1:1 allocation. A postdoctoral researcher not otherwise involved in the study will generate a randomization list using random numbers in Microsoft Excel. A block randomization will be performed with a block size of eight. The study is registered in the German Clinical Trials Register (Deutsches Register Klinischer Studien; DRKS00023007).

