### Participants

Inclusion criteria for participation in the pilot study will be the following: (1) heightened levels of perceived stress as indicated by a score of 19 or above on the Perceived Stress Scale-10 (PSS-10; German version: [66]), (2) at least 18 years of age, and (3) ability and willingness to provide informed consent. Following procedures suggested by Heber and colleagues [67], the PSS cut-off score is set at one standard deviation above the PSS mean score in the validation study of the German version of the PSS-10 [66]. Exclusion criteria will be as follows: (1) the presence of a severe psychological condition (i.e., psychosis; based on self-report), (2) physical conditions impairing the expression of emotion (e.g., facial paralysis), (3) heavy smoking (i.e., more than 10 cigarettes/day due to possible confounding influences on cortisol measures), and (4) suicidal ideation. We expect a medium to large effect size based on previous smartphone-based AAMT studies (e.g., [52, 53]). Therefore, we will include *n* = 10 participants per study group (i.e., *N* = 80 in total) as suggested by Bell and colleagues [68] for pilot studies with expected medium to large effect sizes. To complete the intervention per protocol, participants should attend at least three of the four training sessions. To ensure even distribution of subsample sizes across study conditions, we will change randomization block size in case of treatment dropouts. Number of and reasons for dropping out will be recorded and reported for each condition.

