### Statistical analysis plan

Before conducting the analyses, we will test the preconditions and in case of violations use alternative methods. The level of significance will be set to *α* = 0.05. We will report *p*-values for all analyses.

Feasibility outcomes will be analyzed with descriptive statistics and independent *t*-tests to compare the results of the eAAMT conditions with the swipe control condition. To gain insight into the differences in clinical outcome measures between study conditions, we will compute pre-post effect sizes. In addition, we will conduct exploratory analyses using two-way mixed analyses of variance (ANOVAs) with treatment as between-subjects factor and time as within-subjects factor. Because omnibus tests fail to detect differences between single conditions if the majority of conditions do not differ, we plan to run pairwise comparisons comparing the single eAAMT conditions with the inactive control condition and the swipe control condition. In order to prevent alpha-error accumulation, we will first compare the eAAMT conditions to the inactive control condition. Only if the interaction effect in this comparison will be significant, we will also compare the eAAMT conditions to the swipe control condition. Moreover, as this is a pilot trial and we aim to evaluate if the training is effective in itself, we will conduct per protocol analyses. We will also run intention-to-treat analyses to determine the robustness of the results when considering missing data. All analyses will be conducted in R [91] and SPSS.

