## Discussion

In this pilot study, we will evaluate the feasibility and explore the efficacy of a novel, emotion-based AAMT targeting stress-related beliefs in individuals with elevated perceived stress. Due to their important role in the emergence of perceived stress [20], stress-related beliefs are a promising starting point for interventions against stress. To our knowledge, this is the first study that employs an AAMT with stress-related beliefs as stimuli, thus targeting a construct directly implicated in the process of stress generation. Prior AAMT studies in the stress context that used emotional pictures as stimulus material mostly failed to find effects on stress measures [51, 54]. This demonstrates the need for a new way of designing AAMT interventions against stress, which our study addresses. Another novelty of our intervention is the use of emotions as approach/avoidance responses within an AAMT. Based on assumptions of the inferential account [35], we hypothesize that displaying highly valenced emotional responses within an AAMT will enhance the effects of currently performed AAMTs and be more effective in modifying approach-avoidance biases as well as reducing the particular psychopathology associated with such biases. In addition to their strong valence, the specific appraisals and behavioral tendencies associated with emotions [59] might be transferred to AAMT stimuli, thereby changing their evaluation in a more complex way. Therefore, in our study, participants will display emotional responses to push stress-related beliefs away from themselves and pull stress-reducing beliefs towards themselves. In order to provide an accessible and easy-to-disseminate training, we developed the eAAMT as app-based intervention. Since this is a completely new intervention, we decided to conduct a pilot study in preparation for a larger RCT. With the help of the feasibility evaluation, we will be able to gain insights into how the eAAMT can be implemented and is received by users. Moreover, we will be able to use the information on the feasibility of our study design to make further adaptations before the start of the RCT. By exploring the efficacy of the eAAMT, we will gain preliminary insights into its effects on clinical outcomes and, hence, therapeutic potential. We hypothesize that the eAAMT will be more effective in reducing perceived stress as well as the extent of agreement with dysfunctional beliefs and symptoms of depression than a swipe-based AAMT. In addition to exploring this hypothesis, we will explore whether the display of the emotions anxiety, anger, sadness, or disgust will be particularly effective and whether a bias towards approach responses within the eAAMT increases its efficacy. When we developed the protocol, we decided to use an inactive control condition as one of the comparators. This allows us to answer the question whether the eAAMT is helpful at all. As second comparator, we chose to use the swipe-based AAMT which is currently the most common AAMT variant on the smartphone [39–41, 52, 53]. The comparison with a swipe-based AAMT allows us to investigate whether the use of emotions in the AAMT provides additional benefit.

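### Testing against the inactive control first does not prevent alpha accumulation over six eAAMT arms (about 20-21% per outcome), and it makes the swipe test depend on a low-power gate

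*Protocol article*

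**What the plan says.** The trial randomises to "one of six variants of the eAAMT, an active control intervention (swipe-based AAMT), or an inactive control condition". On size, the Participants section says "we will include *n* = 10 participants per study group (i.e., *N* = 80 in total").

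The Statistical analysis plan section fixes the error rate ("The level of significance will be set to *α* = 0.05") and names the unit of comparison: "we plan to run pairwise comparisons comparing the single eAAMT conditions with the inactive control condition and the swipe control condition". It then gives the error-control device: "In order to prevent alpha-error accumulation, we will first compare the eAAMT conditions to the inactive control condition". The swipe comparison follows only if the interaction against the inactive control is significant. No adjustment over the six arms is stated. The mixed ANOVAs are called exploratory. Pre-post effect sizes are announced before the gate, with no condition attached.

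The Discussion states the hypothesis that the gate controls: "We hypothesize that the eAAMT will be more effective in reducing perceived stress as well as the extent of agreement with dysfunctional beliefs", with the swipe-based AAMT as comparator. On effect size there is only this, in Participants: "We expect a medium to large effect size based on previous smartphone-based AAMT studies".

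**The concern.** A sequence controls error along the sequence. Here it runs from inactive to swipe within an arm, while most of the multiplicity lies across the six arms. A reader who takes the sentence at its word will treat the arm-wise p-values as protected when they are not.

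The gate also decides whether the hypothesis in the Discussion receives an inferential test at all, and that decision rests on a comparison of 10 with 10. If swipe contrasts are shown only for arms that passed, those arms were selected partly because their eAAMT mean happened to be high. Their advantage over swipe is then overstated.

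Finally, the Purpose of the study section asks about the eAAMT as such against each control. The plan names an omnibus ANOVA, which it says can miss differences between single conditions, and single-arm comparisons. It names no contrast of the six eAAMT arms together against a control.

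**Working it through.** **Inputs from the article.** Alpha 0.05 per test; six eAAMT arms, one swipe arm and one inactive arm; 10 per arm. Check of the stated total: 8 × 10 = 80, which reproduces.

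**Assumptions.** Two-sided tests. The group-by-time interaction is represented by a two-sample t test on change scores (10 + 10 − 2 = 18 df). The article says only medium to large, so d = 0.5 to 0.8 is used. No pre-post correlation is given, so r = 0.5 to 0.8 is used.

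**1. False positives in step 1, no arm differing from inactive.**
- If the six tests were independent: 1 − 0.95^6 = 0.265.
- They share one control arm and are positively correlated. Simulation of six t tests against one shared arm of 10 gives 0.207 to 0.208.
- The interaction from a three-time-point mixed ANOVA gives 0.20 to 0.21.

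This result needs no assumption about d, and it hardly changes with r.

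**2. False positives in the swipe step, per-arm gate.**
- No arm differs from either control: about 5%. The gate helps here.
- All eAAMT arms clearly beat inactive but equal swipe: every gate opens, and six unadjusted tests against one shared swipe arm again give about 21%.

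**3. How often the gate opens, per arm.** With d in raw-score SD, the change-score SD is √(2(1 − r)) and the noncentrality is d/√(2(1 − r)) × √(10/2). At r = 0.5 the change SD is 1, so that row is also the result for d in change-score SD.

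| r | change SD | d = 0.5 | d = 0.8 |
|---|---|---|---|
| 0.5 | 1.000 | 18.5% | 39.5% |
| 0.6 | 0.894 | 22% | 47% |
| 0.7 | 0.775 | 28% | 59% |
| 0.8 | 0.632 | 39% | 76% |

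At r = 0.5, no arm opens in about 50% of trials (d = 0.5) or 23% (d = 0.8).

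**4. Selection.** With eAAMT and swipe truly equal, the mean eAAMT-minus-swipe difference among arms that pass is not zero. Over the same grid it runs from about 0.30 SD (d = 0.5, r = 0.5) down to about 0.05 SD (d = 0.8, r = 0.8), in raw-score SD.

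**5. Pooled contrast.** In change-score SD, the SE is √(1/10 + 1/10) = 0.447 for 10 versus 10 and √(1/60 + 1/10) = 0.342 for 60 versus 10. That is a reduction of 1 − 0.342/0.447, about 24%. Unadjusted power, also with d in change-score SD, rises from 19% to 30% (d = 0.5) and from 40% to 64% (d = 0.8). These compare with the r = 0.5 row above, not with the other rows.

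**6. Cost of adjusting.** As an illustration, Bonferroni at 0.05/6 = 0.0083 brings the step 1 family-wise error to 4.1%. Per-arm power falls to about 5% (d = 0.5) and 15% (d = 0.8) in change-score SD.

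**The case against.** The analyses are exploratory, in a pilot that itself concedes a very small sample and leaves efficacy to a larger trial. That stands and lowers the severity. It does not make the sentence about alpha accumulation true.

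The gate is not useless. Testing inactive and then swipe is a valid fixed sequence within an arm, and it stops the second control from adding error when nothing works. That also stands; the defect is the missing control across arms.

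The wording of the gate is partly ambiguous. One pooled test against inactive would hold the first step at 5%, but the section speaks of single conditions, and the six swipe tests behind such a gate could still reach about 20.5%. If any significant arm opened the step for all arms, it would open in about 50% (d = 0.5) to 77% (d = 0.8) of trials at r = 0.5.

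A reader might infer three stronger points, and the article supports none of them:
- That eAAMT versus swipe goes unestimated in most arms. Pre-post effect sizes are planned without any gate, so only the inferential comparison is withheld. Even for that, most arms is not a safe statement: at d = 0.8 in raw-score SD the gate opens in 59% of arms at r = 0.7 and 76% at r = 0.8.
- That biased estimates will feed the planning of the larger trial. Nothing says that planning would use only arms that pass; the upward bias arises only if one selects on the gate.
- That a count of false positives over every outcome and item measures the problem. It presumes no effect anywhere and gives single emotion items the same standing as the one primary outcome, PSS-10.

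**Conclusion.** The claim of error control is wrong as written. Step 1 carries about 20-21% family-wise error per outcome, given only two-sided tests at 0.05, 10 per arm and a shared control. The swipe step reaches about 21% in the scenario that matters most for the stated hypothesis, where emotion-based training works but no better than swiping.

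The second part is conditional. The gate withholds the inferential swipe test in a majority of arms at d = 0.5 for every r tried. At d = 0.8 in raw-score SD it does so for r of 0.5 and 0.6 but not for 0.7 or 0.8. The selection bias of about 0.05 to 0.30 SD applies only to swipe contrasts shown for passing arms alone, with eAAMT and swipe equal. Both ranges rest on assumed d and r.

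Severity: should-fix.

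**What to change.** 1. Delete the statement that the order prevents alpha accumulation, or make it true for PSS-10 by giving Dunnett- or Holm-adjusted p-values over the six arms in each step. If the claim is to cover both controls jointly, apply Holm over all 6 × 2 = 12 contrasts. Label the other outcomes as unadjusted and exploratory.
2. Report every eAAMT-versus-swipe contrast with a 95% CI, whatever the first step shows. If a gate is kept for p-values, state whether it works per arm, on any arm, or on a pooled test.
3. For the aggregate question in Purpose of the study, add two planned contrasts on PSS-10 from one eight-arm model: all eAAMT arms versus inactive, then all eAAMT arms versus swipe, in that order.

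The cost is wording and a few contrast statements, with no new data. There are real downsides. Adjusted arm-wise tests lose power that is already low, and a pooled contrast averages over arms that may differ and does not answer which emotion works best. The arm-wise estimates should therefore stay in the report. The Trial status section describes recruitment as ongoing, so on that account the change could be fixed before analysis.

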To assess *stress-related (dys-)functional beliefs*, a total of ten items were selected from Rojas and colleagues’ [69] short version of the DAS. The DAS was developed as a self-report instrument to assess dysfunctional attitudes that are typically found in depressive patients. The ten items with the best fit for the stress context of the current study were selected by an expert group under supervision of MB: nine statements consisting of dysfunctional attitudes and one of a functional attitude. Then, two versions of the scale were created. The first version assesses the agreement with the ten DAS items on a 7-point Likert scale (DAS-A; 1 = *fully disagree* to 7 = *fully agree*) and the second version the perceived helpfulness of the beliefs (DAS-H; 1 = *not at all helpful* to 7 = *very helpful*). To obtain a total score, the functional-belief item is reversely coded, and the ten items are summed up. The total score in both versions ranges between 10 and 70. A higher score in the DAS-A represents higher agreement with dysfunctional stress-related beliefs, and a higher score in the DAS-H represents a higher helpfulness rating of dysfunctional beliefs.

To assess the *emotional state*, i.e., the intensity of emotions experienced during the last week, a team of experts in the assessment and regulation of emotions extended the German version of the Positive and Negative Affect Schedule [85] in a way that the following affective states are all assessed with one item: courage, gratitude, joy, pride, excitement, resolve, anger, anxiety, sadness, confidence, disgust, tranquility, love, happiness, relaxation, and content. Each item starts with the instruction “During the last week, I felt…” and invites participants to rate the intensity of the respective emotion during the past week on a 5-point Likert scale ranging from 0 = *not at all* to 4 = *very much*. The items will be analyzed separately.

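### The stepwise order said to prevent alpha-error accumulation covers only the second comparator; across the six eAAMT arms the step-1 family-wise error is about 21%

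*Protocol article*

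**What the plan says.** All of this is in the protocol article; no separate analysis plan is shown. The abstract (Methods) lists the arms as "one of six variants of the eAAMT, an active control intervention (swipe-based AAMT), or an inactive control condition". Allocation is equal (Design: "Participants will be randomly assigned to one of the eight study groups with a 1:1 allocation") and the arms are small (Participants: "we will include *n* = 10 participants per study group").

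Under Statistical analysis plan, "The level of significance will be set to *α* = 0.05". The clinical outcomes are explored with two-way mixed ANOVAs, treatment by time. The section argues that omnibus tests can miss differences between individual conditions, and continues: "we plan to run pairwise comparisons comparing the single eAAMT conditions with the inactive control condition and the swipe control condition". The multiplicity measure is then given as: "In order to prevent alpha-error accumulation, we will first compare the eAAMT conditions to the inactive control condition". The second step is conditional: "Only if the interaction effect in this comparison will be significant, we will also compare the eAAMT conditions to the swipe control condition". No other multiplicity measure is described. The same section calls the ANOVAs exploratory, and PSS-10 is the single primary outcome (Clinical outcomes).

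**The concern.** Two sources of multiplicity are present: two comparators, and six eAAMT arms tested in parallel against each. A fixed order with a conditional second step deals with the first source. It cannot deal with the second, because the six step-1 tests run side by side at the full 0.05, and so do the step-2 tests that are allowed to proceed. The protocol nevertheless presents the order as the measure that prevents accumulation, without limiting the claim.

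At stake is how a significant result is read. Which negative emotion works best is one of the protocol's exploratory questions. A reader who accepts the sentence would take a single significant arm as evidence already protected against multiple testing, when it is not.

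**Working it through.** **Inputs.** Six eAAMT arms (abstract); 10 per arm, equal allocation (Participants, Design); 0.05 per test, interaction F test (Statistical analysis plan); three assessments, T1 to T3 (Procedures). Assumptions: two-sided tests, normal data, equal correlation between time points within a person, no missing data. With equal arm sizes, two contrasts sharing a control have correlation 0.5.

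**The plan's own figure.** The plan gives 0.05 as the level of each test and states no family-wise rate. Simulating one arm against the inactive arm (10 v 10, three times, F on 2 and 36 df, no effect) reproduces 0.050 per test.

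**Step 1, six arms against inactive, no true effect.**
- Upper bound: 6 × 0.05 = 30%.
- If the tests were independent: 1 − 0.95^6 = 26.5%.
- With the shared control, normal approximation, c = 1.96: 1 − ∫ [Φ((c + x√0.5)/√0.5) − Φ((−c + x√0.5)/√0.5)]^6 φ(x) dx = 20.7%.
- Simulation, t-tests on 18 df: 20.6%. Mixed-ANOVA interaction with two time points: 20.5%. With three time points: about 21%.

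**Direction.** These rates count an eAAMT arm that looks worse than control as well as one that looks better. Counting only false results in favour of at least one eAAMT arm gives 10.6% for a single contrast. For the three-time interaction it is about 11.0%, taking favourable to mean a better average post-training change.

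**What the order does achieve.** If all twelve tests were run unconditionally with no true effect, the chance of any rejection is 34.4%. If an arm meets swipe only after it has beaten inactive, any step-2 rejection presupposes a step-1 rejection, so the total equals the step-1 rate, 20.6%. The error added by the second comparator is removed; the error across arms remains.

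**Step 2, when the eAAMT arms beat inactive but equal swipe.** Chance of at least one false eAAMT-v-swipe result, either direction (t-tests, 10 per arm), by how the condition for proceeding is read:

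| True difference from inactive | Each arm must pass | Any arm passing suffices | One pooled test must pass |
|---|---|---|---|
| 0.5 SD | 7.9% | 12.6% | 6.3% |
| 0.8 SD | 10.4% | 17.2% | 13.1% |
| 1.0 SD | 12.1% | 19.2% | 16.9% |
| 2.0 SD | 19.9% | 20.7% | 20.7% |
| 3.0 SD | 20.7% | 20.7% | 20.7% |

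**Alternative reading of step 1.** A single pooled test of all eAAMT arms against inactive has error 5.0%. An omnibus test ahead of the pairwise tests would give 3.9% with no true effect, but the section argues against relying on omnibus tests.

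**After adjustment.** Holm's first threshold is 0.05/6 = 0.0083. With no true effect the step-1 family-wise rate is then about 4%.

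**The case against.** The strongest reply is that this is a feasibility pilot. The ANOVAs are labelled exploratory, effect sizes are mentioned before them, and the limitations call the sample very small and defer efficacy to a larger study. Strict family-wise control is not obligatory here. That stands and lowers the severity, but it does not make the sentence correct: the protocol chose to claim protection.

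The wording is also open to a second reading. The conditional sentence refers to one interaction in one comparison, which could mean a pooled test. That would hold 5% at step 1. The preceding plan to compare the single eAAMT conditions makes the pairwise reading the natural one, and under a pooled first step the six swipe tests would still be uncontrolled.

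Several stronger readings are tempting and are not supported:
- A reader might infer that a stated 5% family-wise rate is exceeded fourfold. No such rate is stated; 0.05 is the level of a test.
- A reader might take 21% as the chance of declaring a useless variant effective. In that direction it is about 11%.
- A reader might conclude that the order protects nothing. It does remove the second comparator's contribution when nothing works.
- A reader might extend the charge to all outcomes, since for emotional state and current stress "The items will be analyzed separately". The sentence at issue concerns the two comparators, PSS-10 is the one primary outcome, and unadjusted secondary outcomes are ordinary in an exploratory pilot.
- A reader might suppose that a false positive would decide which variant enters the later trial. The protocol nowhere selects a variant by significance.

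**Conclusion.** The claim of prevention is too broad. On the pairwise reading, the order controls the second comparator under the global null and leaves the six arms unadjusted: about 21% for any false step-1 interaction on PSS-10, about 11% for one favouring an eAAMT arm. Step 2 carries its own error when the eAAMT arms are better than inactive but no better than swipe: 12.1–19.2% at 1 SD with pairwise first-step tests, depending on whether each arm or any arm must pass, with a limit of about 21%.

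These figures rest on equal arms of ten, complete data and one outcome. The parallel per-protocol and intention-to-treat analyses are not counted. The step-1 figure falls to 5% if one pooled test was intended. Severity is minor to moderate: the stated justification needs correcting, while the exploratory design itself is defensible.

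**What to change.** Either change suffices.

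1. For PSS-10, apply Holm to the six treatment-by-time interaction p-values against inactive, and again to the six against swipe. Holm works directly on p-values, so the planned F test stays; Dunnett is built for single contrasts and would not fit a 2-df interaction. This controls each family of six, not the two combined. The cost is lower power per arm. As a guide only, for a single contrast at 0.8 SD (within-person correlation 0.6, 72 df), a Dunnett adjustment takes power from about 51% to 27%. Holm's first threshold (0.0083) is slightly stricter than Dunnett's per-comparison level (about 0.0105).

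2. Reword the sentence to say that the order limits error from the second comparator only. State that p-values are exploratory and unadjusted across the six eAAMT arms, with a family-wise rate of about 21% for the step-1 family. This costs nothing.

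In either case, state whether step 1 is six tests or one pooled test, and whether the condition for proceeding to swipe applies arm by arm.

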### Purpose of the study

Before conducting a large RCT on the eAAMT, we aim to test intervention and study procedures and estimate preliminary effect sizes on clinical outcomes. For this purpose, we will run a pilot study with the following aims: (a) evaluate the feasibility of the intervention and study design and (b) explore its efficacy in influencing clinical outcomes when compared to an inactive control condition and a swipe-based AAMT (swipe control condition). Additional exploratory questions are whether the specific emotions anxiety, anger, sadness, and disgust differ with respect to their effectiveness in eAAMTs and whether deviating from the common 50:50 ratio of approach vs. avoidance responses (e.g., [35, 47]) in favor of a 1:4 bias towards approach responses would lead to stronger effects on the reduction of perceived stress.

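### The eAAMT-v-swipe test is run only after a significant result against the inactive arm, so at 10 v 10 it is made for a selected subset of arms and its estimate there leans towards the eAAMT

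*Protocol article*

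**What the plan says.** Under Purpose of the study, aim (b) is to "explore its efficacy in influencing clinical outcomes when compared to an inactive control condition and a swipe-based AAMT (swipe control condition"), and the same paragraph names the estimation of preliminary effect sizes, ahead of a large RCT, as a goal of the pilot. The Discussion states the hypothesis: "We hypothesize that the eAAMT will be more effective in reducing perceived stress as well as the extent of agreement with dysfunctional beliefs" and depressive symptoms, with the swipe-based training as the comparator. It gives the swipe comparison as the way to learn whether using emotions adds anything.

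On size, the Design section says "Participants will be randomly assigned to one of the eight study groups with a 1:1 allocation", and the Participants section says "We expect a medium to large effect size based on previous smartphone-based AAMT studies" and "Therefore, we will include *n* = 10 participants per study group (i.e., *N* = 80 in total").

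The Statistical analysis plan sets "The level of significance will be set to *α* = 0.05". It first announces pre-post effect sizes, with no condition attached. It then adds exploratory two-way mixed ANOVAs, within which "we plan to run pairwise comparisons comparing the single eAAMT conditions with the inactive control condition and the swipe control condition". To limit alpha accumulation, the inactive comparison comes first, and then: "Only if the interaction effect in this comparison will be significant, we will also compare the eAAMT conditions to the swipe control condition".

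**The concern.** The comparison that carries the hypothesis depends on the success of another low-powered test. Two consequences follow for outcomes taken in all eight arms, such as the PSS-10.

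- At 10 v 10 the first test will often miss an effect of the size the article expects, and then no swipe test is made for that arm.
- The change in a given eAAMT arm enters both contrasts. Arms that pass tend to be those whose change was favourable by chance, and the same chance error is carried into the comparison with swipe.

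At stake is what the pilot hands on to the RCT. A between-arm estimate against swipe that appears only for selected arms, and is too high there on average, is a poor basis for choosing an eAAMT variant or sizing the next trial.

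**Working it through.** **Inputs from the article.** Eight arms, 1:1, n = 10 each: 8 × 10 = 80, the stated total. Alpha is 0.05; sidedness is not stated, and the interaction F-test is non-directional. Clinical outcomes are assessed at T1, T2 and T3. The expected effect is medium to large, with no number.

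**Assumptions.** Medium to large is taken as 0.5 to 0.8 SD against the inactive arm, constant at T2 and T3. Within-person correlation r is 0.5 to 0.7 with compound symmetry. The first step is read arm by arm.

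**Step 1: chance of passing, closed form.** For a pre-post change the SD is √(2(1−r)), so the noncentrality is d/√(2(1−r)) × √(10/2), with 18 degrees of freedom.

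- d = 0.5, r = 0.5: 0.5/1.000 × 2.236 = 1.118, power 18.5%
- d = 0.5, r = 0.7: 0.5/0.775 × 2.236 = 1.443, power 27.7%
- d = 0.8, r = 0.5: 0.8/1.000 × 2.236 = 1.789, power 39.5%
- d = 0.8, r = 0.7: 0.8/0.775 × 2.236 = 2.309, power 58.9%

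**Step 2: the planned test, by simulation.** Each setting used 40,000 trials of six eAAMT arms, one shared swipe arm and one shared inactive arm. The test was the 2-group × 3-time interaction, F(2,36), p < 0.05. eAAMT and swipe were set truly equal. The difference is eAAMT minus swipe in improvement (mean of T2 and T3 minus T1), among arms that passed in the favourable direction.

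| Effect v inactive | r | A given arm passes | No arm of six passes | Mean difference, passing arms (truth 0) | False result for eAAMT, given passing | Same, unconditional |
|---|---|---|---|---|---|---|
| 0.5 SD | 0.5 | 18% | 49% | +0.24 SD | 7.7% | 1.4% |
| 0.5 SD | 0.6 | 22% | 43% | +0.21 SD | 7.1% | 1.5% |
| 0.5 SD | 0.7 | 28% | 34% | +0.16 SD | 6.0% | 1.7% |
| 0.8 SD | 0.5 | 41% | 20% | +0.16 SD | 4.8% | 2.0% |
| 0.8 SD | 0.6 | 50% | 14% | +0.13 SD | 4.3% | 2.1% |
| 0.8 SD | 0.7 | 62% | 7% | +0.08 SD | 3.7% | 2.3% |

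Repeat runs move the last digit by about one. Without the precondition the mean difference is 0.00 SD, and the chance of a false result for the eAAMT is 2.5% per arm, in every row. The six first-step tests share one inactive arm and so succeed or fail together. That is why no arm passes more often than six independent tests would suggest: for the first row, 0.82⁶ = 30% against 49%.

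**Step 3: precision of an unconditional contrast.** The improvement score has variance 1.5(1−r), so the standard error of a 10 v 10 contrast is √(2 × 1.5(1−r)/10). This is 0.387 SD at r = 0.5 and 0.300 SD at r = 0.7. With t = 2.101 (18 df), the 95% half-width is 0.81 or 0.63 SD.

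**Step 4: the other reading.** If all eAAMT arms were pooled for the first step (60 v 10), it would pass in 30–48% of trials at 0.5 SD and 67–88% at 0.8 SD over r = 0.5 to 0.7. The mean difference per arm given passing would then be +0.03 to +0.04 SD and +0.01 to +0.02 SD.

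**The case against.** The order has a rationale. The Discussion uses the inactive arm to ask whether the training helps at all and the swipe arm to ask about added benefit, and the limitations concede that the sample is very small. Several stronger readings are tempting, and the article does not support them.

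- *The eAAMT-v-swipe effect will often be missing altogether.* Not so: pre-post effect sizes are planned without any condition, and the data set is to be made public, so a reader could set the arms side by side. These are within-arm figures, however, and not between-arm contrasts with intervals.
- *The swipe comparison is usually not made.* This holds per arm over much of the assumed range, but not near 0.8 SD with r of 0.6 or more. At r = 0.6 at least one arm passes in about 57% of trials at 0.5 SD and 86% at 0.8 SD.
- *The rule inflates the type I error of the swipe test.* It does not. Taken unconditionally, the chance of a false result for the eAAMT is 1.4–2.3% per arm, below 2.5%. The excess appears only given that the arm has passed.
- *A significant worsening would also open the swipe comparison, so the rule misleads.* True of the wording, but negligible: about 0.2% of arms at most at 0.5 SD, and fewer at 0.8 SD.

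Two further points stand. The conditional sentence does not say outright that it works arm by arm; the reference to single conditions just before makes that the natural reading, and under pooling the bias nearly vanishes. And the bias is smaller than the sampling error of a 10 v 10 contrast throughout.

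**Conclusion.** The concern holds in a limited form. On the arm-by-arm reading, the plan withholds the between-arm test that carries its hypothesis from a given eAAMT arm in roughly 72–82% of cases at 0.5 SD and 37–59% at 0.8 SD. Where the comparison is made, the estimate is biased towards the eAAMT by about 0.16–0.25 SD and 0.08–0.17 SD respectively if eAAMT and swipe are truly equal.

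These figures rest on an assumed correlation of 0.5 to 0.7, a stable effect at T2 and T3, and 0.5 to 0.8 SD as the meaning of medium to large. They describe selection in what is reported, in an analysis the article itself labels exploratory. The plan should be changed because the change is cheap and serves the estimation aim; the trial is not invalidated by leaving it.

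**What to change.** Replace the conditional sentence. Estimate and report the eAAMT-v-swipe contrast, with a 95% CI, for every eAAMT arm and every outcome measured in both arms, whatever the inactive-arm result. Keep the inactive-first order, if wanted, only as the rule for when a difference from swipe may be called significant, and say whether that rule applies arm by arm or to the eAAMT arms jointly.

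The cost is a sentence or two in the plan and a fuller results table; no new data are needed. The downside is more exploratory contrasts with wide intervals (half-width about 0.6 to 0.8 SD under the assumptions above), to be read as estimates and not as tests.
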